## Abstract

**Background:**

Chronic subdural hematoma (cSDH) is one of the most frequent neurosurgical conditions affecting elderly people and is associated with substantial morbidity and mortality. The use of a subdural drain (SDD) after burr-hole trepanation for cSDH was proven to reduce recurrence and mortality at 6 months. To date in neurosurgery practice, evidence-based guidelines on whether an SDD or subperiosteal drain (SPD) should be used do not exist. Currently both methods are being practiced depending on the institute and/or the practicing neurosurgeon.

**Objective:**

The aim of this study is to compare the reoperation rates after burr-hole trepanation and insertion of an SPD or SDD in patients with cSDH.

**Methods:**

This is a prospective, noninferiority, multicenter, randomized controlled trial designed to include 220 patients over the age of 18 years presenting with a symptomatic cSDH verified on cranial computed tomography or magnetic resonance imaging who are to undergo surgical evacuation with burr-hole trepanation. After informed consent is obtained, patients are randomly allocated to an SPD or SDD group. The primary endpoint is recurrence indicating a reoperation within 12 months.

**Results:**

This research is investigator-initiated and has received ethics approval. Patient recruitment started in April 2013, and we expect all study-related activities to be completed by the end of 2016 or beginning of 2017.

**Conclusions:**

To date, evidence-based recommendations concerning the operative treatment of cSDH are sparse. Results of this research are expected to have applications in evidence-based practice for the increasing number of patients suffering from cSDH and possibly lead to more efficient treatment of this disease with fewer postoperative complications.

**Trial Registration:**

ClinicalTrials.gov NCT01869855; https://clinicaltrials.gov/ct2/show/NCT01869855 (Archived by WebCite at http://www.webcitation.org/6fNK4Jlxk)

## Introduction

### Background

Chronic subdural hematoma (cSDH) is one of the most frequent neurosurgical conditions affecting elderly people and is associated with substantial morbidity and mortality [1-3]. Its incidence is reported to be 1.7-13.1 per 100,000 inhabitants per year, but the incidence has been steadily increasing due to prolonged life expectancy [4-6]. Surgical treatment is recommended in patients with neurological symptoms. In the only evidence-based review of the different surgical treatment modalities of cSDH, Weigel et al concluded that burr-hole craniostomy with irrigation and drainage has the best cure-to-complication ratio [7]. Recurrence is the most common complication following surgical treatment of cSDH with a rate of 0%-30% [3,4,8]. A randomized controlled study by Santarius et al showed reduced recurrence and mortality placing a subdural drain (SDD) compared to not placing a drain after burr-hole evacuation of cSDH [2]. Gazzeri et al and Zumofen et al used a closed subperiosteal drain (SPD) instead of the more commonly used SDD, and the method showed equal or superior results in outcome, complications, and postoperative symptoms compared to previous studies [9,10]. Since the SPD is not positioned in direct contact to cortical structures, bridging veins, or hematoma membranes, it is considered safer and might be favorable to an SDD. In a retrospective study, Bellut et al compared 48 patients treated with SPD to 65 patients treated with SDD and found lower mortality rates and fewer serious complications in the group treated with SPD with no difference in recurrence rate of cSDH [5]. However, none of the results showed a significant difference, and it was concluded that further randomized studies with a larger patient cohort are needed [5]. In a recently published prospective randomized study, Kaliaperumal et al concluded that the recurrence rate after placing an SPD is equal to that following placement of an SDD, with the modified Rankin scale (mRS) of the patients in the SPD group being significantly better after 6 months [11]. However, the results may have been biased since the preoperative mRS in the SPD group was inferior to those in the SDD group. In addition, the number of patients studied was small (25 per group), and the overall recurrence rate was 0%, with very low morbidity and mortality rates compared to the literature. Due to these biases the authors recommend further prospective and randomized studies with larger patient cohorts [11].

At the time of this writing, evidence-based guidelines on which method should be used in cSDH do not exist, and both SDDs and SPDs are being used depending on the institute and/or the practicing neurosurgeon.

### Aims and Objectives

The primary objective of our study is to investigate in a randomized controlled fashion whether the recurrence rate after insertion of an SPD is noninferior compared to the insertion of an SDD in patients undergoing surgical evacuation of a cSDH with burr-hole trepanation. The secondary objective of the study is to assess whether the insertion of an SPD leads to fewer operative complications, a lower mortality, and a better outcome.

## Methods

### Trial Design

This is a prospective, multicenter, noninferiority, randomized controlled study. Eligible participants are block-randomized in a 1:1 allocation ratio to one of two arms: an intervention arm, insertion of an SPD and a control arm, insertion of an SDD.

### Study Setting and Selection Criteria

Patients will be recruited from the departments of neurosurgery at Kantonsspital Aarau and University Hospital of Basel in Switzerland. Both centers are major trauma and neurosurgical referral centers. Eligible participants are female or male over the age of 18 years presenting to one of the centers with a symptomatic cSDH diagnosed by computed tomography (CT) and/or magnetic resonance imaging (MRI). Exclusion criteria are as follows: (1) surgeon decides to perform a craniotomy based on any intraoperative condition (eg, acute hematoma), (2) cSDH is caused by an underlying condition (eg, overdrainage of a ventriculoperitoneal shunt), and (3) no informed consent.

### Informed Consent

Written informed consent of the patient or relative must be obtained by a member of the neurosurgical staff prior to randomization. The neurosurgical staff members undergo a trial-specific training making them eligible to include patients in the trial. A written information sheet is given to the patient or relative and as much time as necessary is allowed to discuss the options. If the patient is unable to give consent due to the nature of the hemorrhage, a personal representative is approached to give consent on behalf of the patient. If the patient is unable to consent and a relative or representative of the patient is not available, an independent doctor can consent on behalf of the patient. In such a case, consent by the patient or representative must be sought at a later time or the patient will be excluded from the study. The consent forms (written in German) are filed with the trial documentation.

### Randomization

Randomization with blocks of 30 in an allocation ratio of 1:1 will be performed by the investigators using the Web-based randomization software Random Allocation version 1.0. Instructions on which drain should be implanted are kept in sealed envelopes labeled with sequential study numbers and opened at surgery before the insertion of the drain. The nature of this intervention does not allow for masking of treatment allocation. However, data is encoded and clinicians are masked to outcomes when possible.

### Trial Interventions

All patients undergo surgical evacuation of a symptomatic cSDH with two burr-hole trepanations; an SPD or SDD is then inserted without suction according to the arm of the study to which the patient has been randomized. The surgical procedure is standardized for both institutions and consists of supine positioning of the patients on a horseshoe headrest. The frontal and parietal areas of the head are shaved, and patient is draped. After skin incision, two 13 mm burr-holes about 7 to 8 cm apart are drilled over the maximum width of the hematoma. The dura mater is opened with a cruciate incision and coagulated. The subdural hematoma is then washed out with warm saline with or without a Nelathon catheter. Once the surgeon completes the irrigation and is ready for drain insertion, the randomization envelope is opened and the assigned drain (subdural or subperiosteal) is inserted. The SDD is inserted from the parietal burr-hole in frontal direction under visual control. The SPD is inserted subgalealy and placed over both burr-holes. In case of a subperiosteal insertion, the burr-holes should not be sealed off with any kind of material (eg, PDS-Folie, Spongostan) so that a communication between the subdural space and the SPD is maintained. Bilateral hematomas are treated as one case; both sides receive the same treatment. Patients with crossover treatment (ie, a patient is randomized to SDD but the surgeon feels it is unsafe to insert an SDD because the brain might be injured and inserts an SPD) will be noted in the case report form and will not be excluded from the study. If the surgeon decides intraoperatively to perform a craniotomy (eg, due to clotted hemorrhage which does not evacuate with burr-hole trepanation), the patient will be excluded from the trial.

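### Suitability for both drains is not recorded before the envelope is opened, so patients judged unsafe for a subdural drain are identifiable only in the SDD arm

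*Protocol article*

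**What the plan says.** **Who is eligible.** Study Setting and Selection Criteria states: "Eligible participants are female or male over the age of 18 years presenting to one of the centers with a symptomatic cSDH". Three exclusions follow as a complete list. The first is intraoperative ("surgeon decides to perform a craniotomy based on any intraoperative condition (eg, acute hematoma"), the second concerns the cause ("cSDH is caused by an underlying condition (eg, overdrainage of a ventriculoperitoneal shunt"), and the third is lack of consent. None refers to suitability for both drains.

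**When allocation is revealed.** Trial Interventions: "Once the surgeon completes the irrigation and is ready for drain insertion, the randomization envelope is opened". By then the burr-holes are drilled, the dura is open and the haematoma has been washed out.

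**What happens to crossovers.** The same section describes one direction only, from SDD to SPD: "a patient is randomized to SDD but the surgeon feels it is unsafe to insert an SDD because the brain might be injured", and an SPD goes in instead. These patients "will be noted in the case report form and will not be excluded from the study".

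**How they are analysed.** Statistical Analysis makes ITT the main analysis and adds a per-protocol sensitivity analysis because crossovers are possible. The article gives no expected crossover rate. The 5% allowance under Sample Size names death and loss to follow-up as its examples.

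**The concern.** A patient who would receive an SPD whichever envelope is opened carries no information about drain position. Randomisation puts about the same share of such patients in each arm, but the plan reveals them only where the envelope says SDD. Their counterparts in the SPD arm are never marked.

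This has two consequences. ITT keeps these patients and shrinks the observed difference: that costs power if SPD is better, and makes a noninferiority claim easier if SPD is worse. A per-protocol set that drops crossovers removes them from the SDD arm alone, so the two remaining groups are no longer alike. No later analysis can recover the matching SPD patients, because nothing about them was recorded.

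The protocol opens the envelope late and already accepts one intraoperative exclusion, so it has a natural moment for such a record.

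**Working it through.** **Inputs from Sample Size.** Recurrence 3.5% and 10.5%; margin 3.5 points; two-sided 95% interval by the continuity-corrected Wilson score method; 220 randomised, 208 evaluable, hence 208/2 = 104 per arm; 80% power. The planned power is reproduced only with SPD 3.5% and SDD 10.5%, so that reading is used.

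**Assumptions.** A share *u* of patients is unsuitable for an SDD. All of them receive an SPD if allocated SDD, and they then have the SPD recurrence rate. The article gives neither *u* nor their risk, so a range is shown.

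**Method.** For each arm with observed proportion p and size n, with z = 1.96, the limits are

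L = [2np + z² − 1 − z√(z² − 2 − 1/n + 4p(n(1−p) + 1))] / [2(n + z²)]

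U = [2np + z² + 1 + z√(z² + 2 − 1/n + 4p(n(1−p) − 1))] / [2(n + z²)]

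The upper limit for SPD minus SDD is (p_SPD − p_SDD) + √[(U_SPD − p_SPD)² + (p_SDD − L_SDD)²]. Power is the exact binomial probability that this limit lies below 3.5 points.

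**The plan's own figure.** At 104 per arm and u = 0, power is 78.5%, within 2 points of the stated 80%. The first size to reach 80% is 109 per arm.

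**If SPD is better, as planned.** The SDD-arm rate under ITT is 10.5 − 7u (in %), and the ITT difference is −7(1 − u) points.

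| u | SDD-arm rate | ITT difference | Power, 104 per arm |
|---|---|---|---|
| 0 | 10.50% | −7.00 | 78.5% |
| 5% | 10.15% | −6.65 | 76.1% |
| 10% | 9.80% | −6.30 | 73.6% |
| 20% | 9.10% | −5.60 | 68.0% |

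**If SPD is worse by exactly the margin.** Assume 8.75% v 5.25%, which average 7%, the pooled rate in the blinded review. The SDD-arm rate becomes 5.25 + 3.5u.

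| u | ITT difference | False noninferiority |
|---|---|---|
| 0 | 3.50 | 1.3% |
| 10% | 3.15 | 1.7% |
| 20% | 2.80 | 2.1% |
| 30% | 2.45 | 2.7% |

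The nominal one-sided level is 2.5%. The corrected interval is conservative enough to stay below it at 10% and 20%, and it is passed only at 30%.

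**If unsuitable patients were excluded before opening.** Without replacement, n = 104(1 − u) is 99, 94 and 83 per arm at 5%, 10% and 20%. Power is 76.6%, 73.6% and 67.5%, about the same as keeping them. If the 220 target is kept, power stays at 78.5%, but 220/(1 − u) patients must be operated on: 220/0.9 ≈ 244 at 10% and 220/0.8 = 275 at 20%.

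**The case against.** The strongest reply is that the plan already handles crossover openly. Crossovers are recorded and retained, ITT is primary, and a per-protocol analysis is specified because of them. ITT then compares two policies, SDD first and SPD first, which is a legitimate pragmatic question. The surgeon may decline the allocated drain, so nobody is made to receive one considered unsafe. All of this stands, and it is why the point is an improvement and not an error.

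It also stands that exclusion gains no power unless more patients are operated on. That is a real burden in a two-centre trial whose Monitoring section lists low recruitment as a reason to stop.

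What does not stand is the idea that the per-protocol analysis repairs the matter. Without a record made before allocation, unsuitable patients can be found in one arm only.

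A reader might infer that surgeons have already judged an SDD unsafe when they open the envelope, so that a prior check would prevent most crossovers. The article does not support this. It describes a patient already allocated to SDD and does not say when the judgement is formed. The SDD is placed under visual control, so some of the risk may appear only on insertion. The article does not show what share is foreseeable.

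**Conclusion.** The point holds as a cheap improvement. The plan foresees one-way crossover on the surgeon's judgement, reveals allocation at a moment when at least part of that judgement could be made, and records nothing at that moment.

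In the planning case the loss of power is about 2, 5 and 10 points at an assumed u of 5%, 10% and 20%. The rise in false noninferiority is under 1 point up to 20%. Both rest on assumed crossover shares, on crossovers having the SPD recurrence rate and, for the second, on assumed true rates of 8.75% v 5.25%.

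A reader might infer a larger loss from the rule that information falls with (1 − u)². That rule fits a test against zero, whereas this test is against a 3.5-point margin. It would imply power of 67.9% at 10% and 54.0% at 20%, against 73.6% and 68.0% by exact calculation, so it should not be used here.

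**What to change.** Add one step to Trial Interventions. After irrigation and before the envelope is opened, the surgeon records on the case report form, for every patient, whether either drain could be inserted. What counts as unsuitable remains the surgeon's judgement. Use the record alike in both arms, in one of two ways:

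- **Supporting analysis set, eligibility unchanged.** Define the set of patients recorded as suitable for either drain and report it beside the ITT analysis. The cost is one tick box. The record exists only for patients enrolled from then on.
- **Eligibility condition for new patients.** A patient not suitable for both drains is logged and not randomised, and the unopened envelope stays in sequence. This narrows the population and mixes two eligibility rules, because recruitment has started. It restores the planned power only if 220 are still randomised, which takes about 244 (10%) or 275 (20%) operated patients. Envelopes carry sequential study numbers and identifiers are assigned during recruitment; if these are the same number, the amendment must say how an unused envelope is matched to the next patient.

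The first option is the lighter one for a trial under way. In both, crossovers after the check are recorded and retained as now.

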### Data Collection

To preserve confidentiality all patients are allocated a unique study identifier during the recruitment process that is used on all data collection forms. All study documentation is held in secure offices, and the study researchers operate according to a signed code of confidentiality. All data are entered into a password-secured database by the data managers.

### Participant Timeline

Patient admission.Clinical evaluation and cranial CT (if none exists).Obtain informed consent.If the patient is treated with vitamin K antagonist, preoperative reversal using Beriplex and Konakion is done aiming for a preoperative international normalized ratio of 1.3. In patients treated with Aspirin Cardio or Plavix, the medications should be discontinued and surgery postponed for 5 to 7 days if possible. If emergency surgery is indicated, the Aspirin Cardio or Plavix should be discontinued preoperatively and for 2 to 6 weeks postoperatively depending on the indication for treatment (see step 12).Surgical evacuation of the cSDH with burr-hole trepanation.Randomization: SDD group versus SPD group.Monitoring in the intermediate or intensive care unit.Cranial CT and clinical evaluation 24 hours postoperative.Low-weight molecular heparin in prophylactic dosage is given postoperatively with mobilization of the patient (with the drainage pinched off) after 24 to 48 hours.Drain removal after 36 to 48 hours.Patient discharge after clinical evaluation on postoperative day 5 or later.Resumption of Aspirin Cardio or Plavix no earlier than 2 weeks postoperatively for patients with secondary prophylaxis and 6 weeks postoperatively for patients with primary prophylaxis. Resumption of Marcoumar should be no earlier than 6 weeks postoperatively.Clinical evaluation and cranial CT at the outpatient clinic 6 weeks postoperatively (±2 weeks).Clinical evaluation at the outpatient clinic 12 months postoperatively (±4 weeks).

See Multimedia Appendix 1 for a time schedule of enrollment, interventions, assessments, and visits for participants. The flow diagram (Figure 1) illustrates the key steps of the trial.

**Figure 1 figure1:**
[figure not shown]
Study workflow
mRS: modified Rankin Scale, GOS: Glasgow Outcome Scale, CT: computer tomography,
MRI: magnetic resonance imaging.

### Serious Adverse Events

Serious adverse events (SAEs) are recorded on the SAE form and include any of the following outcomes: death, life threatening events, requirement for a new hospitalization or prolongation of existing hospitalization, recurrent event, or persistent or significant disability caused by the surgical treatment. All SAEs will be reported to the local ethics committee, Ethikkommission Nordwest- und Zentralschweiz (EKNZ), within 7 days.

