### Outcomes

The primary outcome measure is recurrence needing revision surgery within 12 months postoperatively. Secondary outcome measures include: (1) complication (morbidity) within 12 months postoperatively; (2) mortality within 12 months postoperatively; (3) Markwalder Scale, mRS, and Glasgow Outcome Score; and (4) radiological characteristics of postoperative CT images at 24 hours and 6 weeks. On axial CT scans, the midline shift is measured in millimeters at the level of the foramina of Monro and the thickness of the hematoma at the thickest area.

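### The SAE definition counts disability only when it is judged to be caused by the surgery, so some disability may go unreported depending on an attribution made in an open-label trial (minor)

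*Protocol article*

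**What the plan says.** The Serious Adverse Events section lists the qualifying outcomes in one sentence. It opens with "death, life threatening events, requirement for a new hospitalization or prolongation of existing hospitalization", continues with recurrent events, and closes with "persistent or significant disability caused by the surgical treatment". The handling rule follows: "All SAEs will be reported to the local ethics committee", within 7 days.

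On masking, the Randomization section states: "The nature of this intervention does not allow for masking of treatment allocation". It then adds: "However, data is encoded and clinicians are masked to outcomes when possible".

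On prior expectation, the Background says of the SPD that, because it does not touch cortex, bridging veins or hematoma membranes, "it is considered safer and might be favorable to an SDD" (the subdural drain). Aims and Objectives makes fewer operative complications, lower mortality and better outcome with the SPD the secondary objective.

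The Outcomes section lists "1) complication (morbidity) within 12 months postoperatively" as the first secondary outcome, followed by mortality, the three functional scales and CT findings. SAE counts are not on that list.

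**The concern.** An SAE definition normally asks only what happened to the patient; whether the treatment caused it is a separate question, answered afterwards. Here the disability criterion asks both at once. A disability judged to come from the hematoma, or from the patient's other illnesses, does not meet that criterion at all.

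That matters in this trial for two reasons. First, a hematoma can itself cause deficits such as paresis and aphasia, so attribution in these patients is a real judgement. Second, the judgement may be made with the drain known, and the article supplies a mechanism for blaming the subdural drain (SDD) that it does not supply for the SPD. If attribution follows that expectation, disability after an SPD is the more likely to be left out.

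At stake is the completeness of SAE recording and of the only case-by-case report of harm to an outside body that the article describes.

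**Working it through.** The plan states no figure on this point, so there is nothing to reproduce. The check sets the sections side by side and then gives an illustration of size.

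**1. Which criteria carry a causal condition?** On the natural reading, the qualifier belongs to the last item only.

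| SAE criterion | Causal condition |
|---|---|
| Death | No |
| Life-threatening event | No |
| New or prolonged hospitalization | No |
| Recurrent event | No |
| Persistent or significant disability | Yes |

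**2. Which disability is exposed?** Only disability that meets none of the first four criteria. A postoperative deficit that lengthens the stay or leads to readmission is an SAE whatever its cause. A deficit first recognised as persistent at the 6-week or 12-month outpatient visit (Participant Timeline) need involve neither. For that patient the causally qualified criterion may be the only route to SAE status.

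**3. Who judges, and knowing what?** The Serious Adverse Events section names no assessor. The masking sentence in Randomization speaks of clinicians masked to outcomes, not to allocation, and is not linked to SAE attribution. Masked attribution is neither stated nor excluded.

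**4. Where else is disability recorded?** Under Statistical Analysis, the mRS, Glasgow Outcome Score, Markwalder score, neurological condition and complications (aphasia and paresis among the examples) are collected at 24 hours, discharge, 6 weeks and 12 months. None has a causal condition. These ratings may also be made with the drain known, but that is a separate matter from the filter.

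**5. How large could the effect be?** Illustration only.

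- n per arm = 208 / 2 = 104 (208 evaluable patients, Sample Size section).
- d = true rate of exposed disability, equal in both arms (assumed).
- a = probability that a case is attributed to surgery, by arm (assumed).
- Expected recorded cases = n × d × a. Expected unrecorded cases = n × d × (1 − a).
- The last column is the exact chance that a two-sided Fisher test gives P < .05. No such test is planned; it serves only as a yardstick.

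| d | a, SDD v SPD | Recorded, SDD v SPD | Chance of P < .05 |
|---|---|---|---|
| 10% | 50% v 50% | 5.2 v 5.2 | 0.02 |
| 10% | 60% v 40% | 6.2 v 4.2 | 0.05 |
| 10% | 70% v 30% | 7.3 v 3.1 | 0.16 |
| 5% | 70% v 30% | 3.6 v 1.6 | 0.04 |
| 20% | 70% v 30% | 14.6 v 6.2 | 0.40 |

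For example, at d = 10% and 70% v 30%: 104 × 0.10 × 0.70 = 7.28 and 104 × 0.10 × 0.30 = 3.12.

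Two things follow. Completeness depends on the average attribution rate: in all three rows at d = 10% it is 50%, so 208 × 0.10 × 0.50 = 10.4 cases go unrecorded under this criterion, even when the arms are treated alike. A difference between arms depends on the gap in attribution, and a large gap is needed before it would show.

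**The case against.** The case on the other side is strong on consequences.

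- **No by-arm SAE comparison is stated.** SAEs appear only as a form and a report. The outcomes, the statistical analysis and the yearly interim analysis rest on recurrence, morbidity, mortality, functional scales and CT findings. A reader might infer that the filter creates a spurious safety advantage for the SPD in the trial's results. The article does not support that. This part of the objection stands.
- **Disability is captured elsewhere.** A reader might infer that an unrelated verdict cannot be reviewed later. It can: a paresis or a worse mRS stays on the case report form, and the Monitoring section has those forms inspected yearly. This stands too, although the scales do not go to the ethics committee within 7 days.
- **The assessor is not named.** A reader might infer that unmasked surgeons apply the filter. That is plausible in an open trial but not stated. What can be said is that no masked assessor is stated.
- **The scope is narrow.** A reader might take the qualifier to cover every item in the list. The sentence permits this, but the natural reading ties it to disability alone, and the other criteria then catch much serious disability.
- **This is a condensed article.** Who assesses causality, and whether the SAE form has a relatedness field, may be settled in the full protocol. Their absence here is no fault. The point rests on the definition as written, which is a stated rule.

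None of this removes the rule itself. A disability that meets no other criterion and is judged unrelated is not an SAE under this text.

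**Conclusion.** The point holds as a minor defect of the safety definition. One SAE criterion merges seriousness with causality, and in an open trial with a stated expectation about which drain is safer, that may leave some disability unrecorded as an SAE and unreported to the ethics committee, possibly more often after an SPD.

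The primary outcome, sample size, noninferiority analysis and listed secondary outcomes are unaffected. The size of any attribution gap is unknown, and every rate in the illustration is assumed. At 10% exposed disability, a 60% v 40% gap moves the expected counts only to 6.2 v 4.2, and even 70% v 30% gives a 0.16 chance of a nominally significant difference. Those figures show that the mechanism is possible; they are no evidence that it operates here.

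The conclusion rests on the natural reading of the sentence. If the qualifier was meant for the whole list, the filter would be wider; the proposed wording removes that ambiguity as well.

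**What to change.** In the Serious Adverse Events section, delete the causal qualifier, that is, the last five words of "persistent or significant disability caused by the surgical treatment". Keep every other item, including recurrent event. Each listed event is then recorded and reported whatever its cause.

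Record relatedness to the drain or the surgery as a separate item, preferably judged by an assessor masked to arm. If the SAE form already has such a field, only the deletion is needed. If SAEs are ever tabulated by arm, show all SAEs first and related SAEs second.

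The cost is one phrase, at most one form field, and somewhat more SAE reports, many of them due to comorbidity in an elderly population.
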